## Abstract

**Background:**

Denture-related stomatitis (DS) is chronic multifactorial inflammation, strongly related to the presence of the biofilm that is the complex structure formed by microorganisms held together by a mucus-like matrix of carbohydrate that adheres to different surfaces, including the denture surface. DS has recently been correlated with deleterious cardiovascular alterations. The potential effect of hygiene protocols in the control of DS and randomized clinical trials that address this oral condition with cardiovascular complications are important in clinical decision-making.

**Material/design:**

A clinical trial, randomized, double-blind, and with parallel groups, will be conducted in Brazil The sample will consist of 100 patients without teeth in both arches, users of at least maxillary complete dentures, and diagnosed with DS, who will be allocated to groups (*n* = 25 per group) according to the different hygiene protocols: (1) brushing of the palate and immersion of the prosthesis in 0.25% sodium hypochlorite solution (positive control); (2) brushing of the palate and immersion of the prosthesis in 0.15% triclosan solution; (3) brushing of the palate and immersion of the prosthesis in lactose monohydrate; or (4) brushing the palate with citric acid and immersing the prosthesis in lactose monohydrate. The response variables will be heart rate variability and alteration of blood pressure (systemic level), remission of DS, removal of biofilm, reduction of microbial load (colony-forming units (CFU)), mouth and prosthesis odor level, expression of MUC1, proinflammatory cytokines, C-reactive protein (CRP), viscosity, pH and salivary flow (locally); patient-centred qualitative analysis will also be undertaken. Measurements will be performed at baseline and 10 days after the interventions. The results obtained will be statistically analyzed as pertinent, with a level of significance of 0.05.

**Discussion:**

This study will provide a guideline for clinical practice regarding the use of hygiene protocols in the treatment of oral diseases (DS) mediated by biofilm. Also, it may provide evidence of correlation of oral manifestation with cardiac risk.

**Trial registration:**

Brazilian Registry of Clinical Trials, RBR-4hhwjb. Registered on 9 November 2018.

## Background

The elderly population continues to expand, and today there are about 810 million people age 60 years and older in the world. By 2050, this number could reach 2 billion (22% of the global population). Intrinsic and extrinsic factors may promote decline in oral health, leading to tooth loss [1], and edentulism or complete tooth loss would be the final consequence of oral disease [2].

Complete dentures are a widely used option in the rehabilitation of the stomatognathic system [3] and may be associated with denture-related stomatitis (DS). *Candida albicans*, a common microorganism of the microflora of the oral cavity in humans, is often found in the biofilm of total dentures [4, 5]. However, in the presence of dentures and favorable conditions, such as biofilm, low salivary pH, regular sugar consumption and alterations in the local immune system (reduction of the activity of salivary antimicrobial enzymes, increase in transformer growth factor β and levels of nitric oxide), *C. albicans* becomes an opportunistic pathogen that leads to DS [6], and also may trigger halitosis [7].

DS is the most commonly found oral manifestation and the main indicator of poor oral health among the edentulous population, affecting one in three individuals using removable dentures [8]. DS is chronic multifactorial inflammation associated with the continuous use of maladaptive prostheses, hyposalivation, and poor hygiene; it is considered one of the main factors responsible for the evolution of inflammation due to the prevalence of *Candida* spp. [2, 9–12].

This inflammation can affect the individuals’ quality of life, since the clinical signs include erythema and edema of the palate mucosa, combined in some situations with subjective symptoms, such as dysgeusia (change in taste sensation) and burning sensation [8, 9, 13, 14]. However, in some patients, non-specificity of symptoms makes this disease often undiagnosed and untreated for long periods [15]. Furthermore, although considered to have little overall impact in terms of mortality/morbidity, early diagnosis and correct treatment may avoid potentiation of the immune response at other sites and/or systemic consequence [1, 16, 17].

Local inflammation associated, or not, with a biofilm, which is a complex structure formed by microorganisms held together by a mucus-like matrix of carbohydrate that adheres to different surfaces, including the denture surface [10], may trigger activation of monocytes and T cells, with overproduction of cytokines, such as interleukin (IL)-6, interferon γ, C-reactive protein (CRP) [17], tumor necrosis factor (TNF)-α and other proinflammatory cytokines, subsequently leading to atherosclerosis and hypertension, with increased cardiovascular risk [17, 18].

The relationship among stomatitis, *C. albicans* infection, and systemic inflammatory response is a recent finding and has not yet been clarified. Maciag et al. [16] analyzed peripheral blood immune cell activation to evaluate whether antifungal treatment of local inflammation caused by DS would influence the systemic immune response [16]. The authors did not find evidence of response complex immune mechanisms involved in the defense against oral fungal infection, though they verified a possible systemic inflammatory response to the topical application of nystatin, a macrolide polyene antifungal agent [17, 18]. Although transient and not intense, this effect should be considered a clinically important finding, since patients with DS are generally elderly, and as such, more susceptible to changes in the immune function. Since IL-1β is a proinflammatory cytokine in this susceptible population, even at a low level of production, this non-physiological outcome can influence the risk of inflammatory diseases, such as atherosclerosis or rheumatoid arthritis.

Osmenda et al. [17] evaluated the clinical relationship between DS treatment and endothelial dysfunction, as local inflammation in the oral cavity may cause the production of anti-inflammatory and proinflammatory cytokines, triggering systemic inflammation and activation of an immune response. The results indicate that DS treatment improved the endothelial function, the deterioration in which is known to precede the development of serious cardiovascular disorders, such as atherosclerosis and hypertension.

The evaluation of the predisposition of the individual with local inflammation to develop systemic diseases can be assessed through the detection of salivary mucins, which play an important role in the protection of buccal mucosa against mechanical and microbial aggression, and the residual saliva presenting higher amounts of mucins compared to total saliva. Recently, the correlation between salivary glycoprotein expression (MUC1, MUC5B, and MUC7) and buccal candidiasis has been suggested. These glycoproteins are responsible for the lubrication and protection of the oral tissues; they also can act in the modulation of the response of microorganisms [19, 20].

Glycosylated transmembrane mucins, such as MUC1, are known as the second line of defense, possibly acting as sensors for any disturbance in the environment, signaling this information into the cell [20, 21], and interacting with local bacteria [22], acting as a barrier for opportunistic infections, against several bacterial strains. At this time, the microorganisms of the dental biofilm are disseminated into the systemic circulation, through the invasion of the gingival tissue throughout the ulcerated epithelium [23]. Also, several proinflammatory cytokines, produced by local inflammation, can reach the systemic circulation [24]; thus, justifying the correlation between stomatitis and systemic diseases.

Heart rate variability (HRV) is one of the reliable and non-invasive approaches used to evaluate the autonomic control of the cardiovascular system in healthy individuals and in patients with the cardiovascular disorder [25]. Although there is no consensus on correlation between sympathovagal modulation and chronic inflammatory processes, there might be correlation between the vagus nerve and inflammation through two pathways. The first one is through the activation of the pituitary-hypothalamic-adrenal axis, resulting in systemic secretion of cortisol, which reduces the inflammation. The second one is through the vagal and sympathetic branches that reach the spleen, reflecting cholinergic and then noradrenergic signals, triggering splenic T cells via adrenergic receptors. These memory T cells will secrete the vagal neurotransmitter acetylcholine, which is responsible for the innate immune response, and which binds to the alpha-7 nicotinic acetylcholine receptor (nAChR) in monocytes, resulting in inhibition of the synthesis of inflammatory cytokines [26]. Together, these two pathways constitute the vagal anti-inflammatory reflex [27].

Scientific evidence of correlation among the biofilm, DS, cardiovascular disease, and adequate denture-related stomatitis treatment may contribute to the establishment of a protocol for the prevention and treatment of local inflammation, to be applied in primary care, which could significantly impact public health costs and patients’ quality of life. To our knowledge, this is the first proposal of a clinical, controlled, randomized, and double-blind study that proposes to test for correlation between treatment of DS, through hygiene and brushing solutions, and local and systemic inflammatory responses and cardiovascular impairment.

### Study hypothesis

The primary null hypothesis of the trial is that there is no difference between the protocols for the prevention and treatment of local and systemic inflammatory responses and cardiovascular risk.

## Methods

### Study setting

A randomized, controlled, double-blind, clinical trial, with parallel groups named according to each hygiene protocol will be performed (Fig. 1). Figure 2 shows the study timeline, according to the Standard Protocol Items: Recommendations for Interventional Trials (SPIRIT) diagram. Additional file 1 presents the SPIRIT checklist.

**Fig. 1 Fig1:**
[figure not shown]
Flowchart of the randomized clinical trial (RCT) (adapted from the Consolidated Standards of Reporting Trials (CONSORT) statement). For each follow up, numbers of withdrawn and lost participants will be reported with reasons. G, group; SH, sodium hypochlorite

**Fig. 2 Fig2:**
[figure not shown]
Study schedule: enrollment, allocation, baseline, interventions, and post-intervention assessments. OHIP-EDENT, Oral Health Impact Profile for edentulous people

The sample will be of convenience, consisting of patients with complete dentures who routinely attend the School of DEntistry of Ribeirão Preto - University of São Paulo (FORP/USP).

### Eligibility criteria

#### Inclusion criteria

The inclusion criteria are as follows: (1) patients may be of either sex; (2) patients must have good general health; (3) patients must be without teeth in both arches, users of upper and lower conventional complete prostheses, or, necessarily, users of a complete upper prosthesis (although edentulous mandibular) in good condition [28]; (4) prosthesis must be made from thermally polymerized acrylic resin and acrylic teeth; (5) patients must present with DS types IB, II, or III, according to the Newton Modified Classification [10]; and (6) their prostheses should present with biofilm with a score equal to, or greater than 1, according to Additive Index Exclusion criteria.

The following patients will be excluded: those patients who (1) present with prostheses with adaptation problems, failures, repairs, or fractures; (2) have allergy to any of the products studied; (3) have severe/serious illness that requires frequent hospitalization; (4) have systemic conditions favorable to the development of *Candida* spp.; (5) have used antibiotic, anti-inflammatory, or antifungal agents in the 4 weeks prior to the study; (6) have other lesions on the oral mucosa; (7) are already practicing palatal mucous brushing at recruitment; and (8) use replacement prostheses during the experimental period.

### Planned interventions

All patients will receive verbal and written instructions according to the hygiene protocols: they should brush the palate region with a soft toothbrush and water for 2 min, once a day (Toothbrush CS 5460C Adulto Ultra Macia, Curaprox, Curaden Swiss do Brasil Imp. Exp. LTDA, São Caetano do Sul, São Paulo, Brasil); immerse their dentures in the specific product once a day for the length of time proposed by the manufacturer; and brush the prosthesis for 2 min using a specific brush (Prosthesis Brush BDC150/152/153, Curaprox, Curaden Swiss do Brasil Imp. Exp. LTDA, São Caetano do Sul, São Paulo, Brazil) and neutral soap, three times a day. In addition, all patients will be instructed to remove the prosthesis during the night and leave it in a container with clean water, and in the morning to rinse the prosthesis under running water before inserting it into the oral cavity. Neutral soap and the solutions will be available to participants in identical dosing vials and in sufficient quantity for continuous use for 10 days; for greater control and monitoring of the hygiene protocol. citric acid in the form of an effervescent tablet will be removed from the package and placed in neutral packaging.

The parallel groups as determined by the different hygiene protocols will each consist of 25 participants. The protocols are as follows:
Group 1 (G1 (control group)) - brushing the palate with a soft brush and prosthesis immersion in 0.25% sodium hypochlorite solution (control group)Group 2 (G2) - brushing the palate with a soft brush and prosthesis immersion in 0.15% triclosan solutionGroup 3 (G3) - brushing the palate with a soft brush and prosthesis immersion in citric acid (Nitradine, Bonyf AG, Liechtenstein, Switzerland)Group 4 (G4) - prosthesis immersion and brushing of the palate with citric acid and a soft brush (Nitradine, Bonyf AG, Liechtenstein, Switzerland)

The risk of adverse effects is low, although the use of palatal brushing may promote trauma in the case of excessive force. If the patient has a complaint about the products under investigation or adverse events, they may interrupt the treatment at any time, and notify us of what has happened. To verify if the patient is performing the protocol and minimizing any risks, there will be a consultation 5 days after the beginning of the treatment, for clarification of doubts and follow up. We expect good adherence due to the provision of an effective treatment modality as a major benefit combined with the need for routine clinical attendance at the School of Dentistry of Ribeirão Preto, and the fact that the provision will be made for post-trial care. We will also remind participants by telephone a few days before each follow-up appointment.

The patients will be instructed to avoid the consumption of beverages or foods that alter the metabolism, such as coffee, soda, alcohol, and chocolate, and to avoid physical exercise 24 h before the tests.

### Randomization, allocation, and blinding

The study will be double-blind, and to achieve this, each researcher (R) will have an assignment during the experiment: participants will be distributed into groups taking into account a random numerical sequence (on a 1:1:1:1 ratio) generated by a computer; a researcher (R1) who is not involved in the clinical steps will place the patients’ identification numbers in an envelope, using a blinded approach, and also will prepare the products. Another researcher (R2) will be responsible for opening the envelope at the moment of the delivery of the appropriate product to the patients, according to the hygiene protocols, and examine the patients and collect samples. A third researcher (R3) will distribute the protocols and orientate the participant, and finally the researcher R4 will perform blinded statistical analysis of the data. The researchers involved in the clinical steps (R2 and R3) and the patients will not be blinded because of the nature of the intervention. Patients’ allocated interventions will not be revealed until the statistical analysis is completed.

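### The trial is called double-blind, but patients and both clinical researchers are stated to be unblinded, and the researcher who opens the envelope also collects the day-10 samples

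*Protocol article*

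**What the plan says.** The label appears in four places in the protocol article. The Abstract has "A clinical trial, randomized, double-blind, and with parallel groups, will be conducted in Brazil" and Study setting has "A randomized, controlled, double-blind, clinical trial, with parallel groups". The last paragraph of the Background uses the term when it claims the study is the first of its kind. The section on randomization, allocation and blinding begins: "The study will be double-blind, and to achieve this, each researcher (R) will have an assignment during the experiment".

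The same paragraph then gives the roles. On the envelope: "Another researcher (R2) will be responsible for opening the envelope at the moment of the delivery of the appropriate product to the patients". R2 is also to "and examine the patients and collect samples". R3 hands out the protocols and instructs the participants, and R4 analyses the data blinded. On blinding status it says: "The researchers involved in the clinical steps (R2 and R3) and the patients will not be blinded because of the nature of the intervention". It closes by saying that patients' "allocated interventions will not be revealed until the statistical analysis is completed".

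Three other sections bear on the point:
- Planned interventions puts soap and solutions in identical vials and the effervescent tablet in neutral packaging.
- The primary outcome section has two blinded, trained researchers score the palate photographs.
- Statistical analysis says that data entry, as well as analysis, is blinded.

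**The concern.** A reader who sees the label will assume that at least the patients and those who examine them do not know the arm. The protocol says the opposite about both. The reason given, the nature of the intervention, explains why patients and R3 might know the product. It does not explain why the person who takes the samples has to know it.

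What is at stake is detection bias in between-arm comparisons. Biofilm yield from palate and denture can depend on how the sample is taken, and a collector who knows the arm may sample differently by arm without meaning to. Patients who know their product may rate symptoms and quality of life differently. The label would present these outcomes as protected when they are not.

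**Working it through.** No arithmetic applies. The check sets the statements side by side.

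**1. Who is stated to be blinded**

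| Party | Task | Stated status | Section |
|---|---|---|---|
| Patients | Use product, report outcomes | Not blinded, but packaging is masked | Randomization; Planned interventions |
| R2 | Opens envelope, examines, samples | Not blinded | Randomization |
| R3 | Hands out protocols, instructs | Not blinded | Randomization |
| Photograph raters | Score the primary outcome | Blinded | Study outcomes, Primary |
| Data entry | Enters data | Blinded | Statistical analysis |
| R4 | Analyses data | Blinded | Randomization; Statistical analysis |
| Laboratory readers | CFU counts, ELISA | Not stated | Local parameters |

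The patients, and the researchers who deal with them directly, are all in the unblinded rows. The label therefore conflicts with the paragraph meant to explain it.

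**2. When R2 learns the arm.** The envelope is opened when the product is delivered. Baseline examination and sampling may come before that. The day-10 visit comes after it, so R2 samples at day 10 knowing the arm, in all four groups (4 × 25 = 100 planned patients).

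**3. Which outcomes this reaches**
- *DS remission (primary):* scored from standardized photographs by blinded raters. Who takes the photographs is not stated.
- *CFU:* palate and denture biofilm must be physically collected, and sample collection is R2's task. Exposed at collection.
- *Saliva measures:* collection is exposed in the same way. The ELISA and other laboratory readings are less open to influence.
- *OHIP-EDENT and VAS:* reported at days 10 and 30 by patients declared unblinded. Exposed, unless the masked packaging in fact keeps patients unaware. These measures sit under sample characterization, but Statistical analysis names OHIP-EDENT as an outcome to be adjusted for its baseline value.
- *Blood pressure and heart rate variability:* automated device and software-processed recordings. Less exposed.
- *Odour:* a device score, with no operator named.

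**4. Can R2 be kept unaware?** R3 is already unblinded and already deals with the patient over the product. Giving the envelope to R3 would unblind nobody new and need no extra staff.

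**5. Is there still time?** Trial status gives September 2018 as the start of recruitment and says clinical results are being analysed. A change of roles can reach few patients, if any.

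**The case against.** The strongest reply is that the protection matters most for the primary outcome, and there it is in place: blinded raters, blinded data entry and a blinded statistician. Several secondary outcomes come from instruments or assays. Identical vials and neutral packaging show that some masking of patients was intended, so the sentence declaring them unblinded may itself be the inaccurate one. The closing sentence on allocation can be read as withholding it only from those who are still blinded, such as R4 and the raters.

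Most of this stands, and it narrows the point. It does not rescue the label: the document never defines double-blind as raters plus statistician, and R2's dual role is stated outright.

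Some stronger readings are tempting but not supported:
- *The primary outcome is assessed unblinded.* The document says the reverse about scoring.
- *Nothing beyond photograph scoring and analysis is blinded.* Data entry is also stated to be blinded, and silence about laboratory readers in a condensed article is not a statement that they know the arm.
- *The closing sentence is a flat contradiction.* It is ambiguous and needs clarifying.
- *R2 takes the odour readings.* No section says so.
- *A number can be put on the bias.* The document gives no figure from which to derive one.

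**Conclusion.** The point holds in limited form. The double-blind label is wrong as written, because the protocol itself says that patients, R2 and R3 are unblinded. Giving R2 both the envelope and the day-10 sampling is an avoidable weakness in the design. It affects CFU and saliva collection, and patients' unblinded status affects OHIP-EDENT and VAS, across all 100 planned patients. The size and direction of any bias cannot be derived.

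This rests on two assumptions: that the samples R2 collects include the biofilm and saliva specimens described under Local parameters, and that the Randomization section describes the patients' status correctly despite the masked packaging. If the second fails, the patient-reported outcomes are better protected than stated, but R2's position does not change. Scoring of the primary outcome is not called into question.

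**What to change.** 1. Replace double-blind in all four places with a statement of who is blinded (the two photograph raters, data entry and the statistician) and who is not (R2, R3 and, once the Randomization section is reconciled with the identical vials and neutral packaging, the patients).
2. Reword the closing sentence of the Randomization section to say from whom allocation is withheld until the analysis is complete.
3. For any patients still to be treated or assessed, have R3 open the envelope and hand over the product, so that R2 examines and samples without knowing the arm. This helps only where R2 has not already learned it.
4. For data already collected, disclose that R2 knew the arm at day 10, and interpret CFU and patient-reported outcomes as not protected by blinding. Extending that to every laboratory assay or instrument reading would go too far.

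The cost is wording, one sentence of disclosure and, where still possible, one task moved between two existing researchers. The double-blind claim is lost, including in the Background's statement of novelty.
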